### Outcomes

*Primary Outcome Measure*

The success of the intervention is defined as statistically significant more reduction in mean score of PSS-10 in the intervention group as compared with the control group at 12 weeks. The primary outcome measure will be Perceived Stress Scale-10 Items (PSS-10). The PSS-10 is a ten item self-reported scale to assess respondents’ global level of perceived stress (36). Respondents were required to rate the frequency of certain feelings they experienced over the past month on a 5-point Likert Scale (1=never, 2=rarely, 3=sometimes, 4=often, 5=always). It has shown to predict the range of health-related outcomes presumed to be associated with appraised stress (36). The PSS-10 has been translated in Chinese and shown acceptable reliability and validity in both adults (37, 38) and adolescents (39).

*Secondary Outcome Measures*

For secondary outcome meansures, the success of the intervention is defined as statistically significant more reduction in mean score of DASS-21 and statistically significant more increase in mean score of ORS and CISS-SFC in the intervention group as compared with the control group at 12 weeks. Negative mental health outcome will be measured using Depression, Anxiety and Stress Scale (DASS-21). DASS-21 consists of 21 items. Each item is rated on a 4 Likert scale ranging from 0 to 3, indicating to what degree each statement applied to participants over the past week. Summed scores range from 0-42 with more severe symptoms indicated by higher scores. This study will utilize total scores in addition to subscale scores. DASS-21 has been validated in Chinese adolescents and proved to have satisfactory psychometric properties in Chinese adolescent population (40).

Positive mental health status will be measured using Outcome rating scale (ORS). The ORS is a four-item self-report instrument. The ORS was developed as a brief alternative to the Outcome Questionnaire-45 (OQ-45)-a widely used and well-validated measure (41). The ORS was designed to assess change in three areas of client functioning generally considered valid indicators of treatment progress: individual (or symptomatic) functioning, interpersonal relationships, and social role performance (work adjustment, quality of life). The ORS was found to have adequate reliability and validity (42). The Chinese version of the ORS was recently validated in Chinese sample and showed to be a reliable and valid measure for Chinese sample and sub-clinical clients (43).

Stress coping behaviors will be measured using the short form of Coping Inventory for Stressful Situations (CISS-SFC). The CISS-SFC is a 21-item scale which measures three dimensions of coping-task-oriented coping, emotion-oriented coping, and avoidance-oriented coping. CISS-SFC has been translated into Chinese and approved to be satisfactorily valid and reliable among Chinese university students (44).

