# Introduction

## Background and rationale

Adolescence is a transitional period with rapid physical and psychosocial changes, which is a developmental period sensitive to stress (1). It is worth noting that levels of stress seem to increase from preadolescence to adolescence (2) and combine with inadequate coping, may induce stress’s well-known effects (3-5). Stress and mental health problems are strongly and significantly correlated for school students (6). Previous studies suggested that stress forms a non-specific risk factor for a wide range of mental health issues, behavioural problems and conduct disorders among adolescents (7-15). Adolescents who are stressed are at higher risk of a wide range of mental health conditions such as anxiety, depression (16), bipolar disorder (16), schizophrenia (16), eating disorders (17), personality disorders (16) and even suicide (18). Those mental health conditions were cited by adolescents as the second-most cited barriers to achieving study goals (19). High school students who experience negative affects and engage maladaptive coping are more likely have lower GPA (20). School related academic stress and burnout decreases student academic motivation and increases the risk for dropout (21, 22). Among adolescents, stress level is also associated with risky behaviours. Moderate- and high-level stress is associated with gaming addition among adolescents (23), and affects their family and social relationships, self-control and self-regulation, as well as academic performance (24, 25).

Managing stress among adolescents is considered to be critical to preventing mental health issues.

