### Interventions

The intervention group will download a stress-managing app, the app can be used on mobile devices including mobile phones and tablets etc. The app will be based on Stress Inoculation Training (SIT) developed by Meichenbaum (29). Even though SIT was designed for military settings, there has been a lot of studies which adapted the SIT and use it among students and adolescents (30-34) and delivered SIT via technologies (35). Our study will modify SIT to high school context by adding assertiveness and training participants cognitive and behavioural techniques to deal with stressors arising from academic environment and peer interpersonal relationships. The online stress-managing intervention will comprise of 11 sessions which consist of psychoeducation, problem assessments, training of stress coping skills (emotion-focused coping skills and problem-focused coping skills), cognitive restructuring, imagery and behavioural rehearsal and role play (see [Appendix 1](#_Appendix_1) for details of the intervention content). The intervention content will be in Chinese language. The control group will not be given access to the app until the termination of the trial (12 weeks after the start of the trial). There will be no other intervention given to the control group. Both the intervention group and the control group will have full access to usual care, which is the psychological courses arranged by the high schools.

The criteria for discontinuing for a given trial participant include: (i) if they self-reported or reported by others to be suicidal; (ii) if they drop out of school during the intervention period; (iii) if they require to withdraw from the study.

Strategies to improve adherence to intervention protocol include:

- Instructions about the importance of following study guidelines for adherence to once weekly product.
- Instructions about the purpose and use of the intervention app.
- Notification sent via app weekly on each Sunday that there will be a session taken in the app.
- Successfully completion of each session will generate a virtual star in the participant’s account as a reward for the participation.
- Adherence assessments include log in times and other usage data collected in the app.

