Negative mental health outcome (i.e., anxiety, depression and stress) will be measured using Depression, Anxiety and Stress Scale (DASS-21). DASS-21 consists of 21 items. Each item is rated on a 4 Likert scale ranging from 0 to 3, indicating to what degree each statement applied to participants over the past week. Summed scores range from 0-42 with more severe symptoms indicated by higher scores. This study will utilize total scores in addition to subscale scores. DASS-21 has been validated in Chinese adolescents and proved to have satisfactory psychometric properties in Chinese adolescent population (40).

Positive mental health status will be measured using Outcome rating scale (ORS). The ORS is a four-item self-report instrument. The ORS was developed as a brief alternative to the Outcome Questionnaire-45 (OQ-45)-a widely used and well-validated measure (41). The ORS was designed to assess change in three areas of client functioning generally considered valid indicators of treatment progress: individual (or symptomatic) functioning, interpersonal relationships, and social role performance (work adjustment, quality of life). The ORS was found to have adequate reliability and validity (42). The Chinese version of the ORS was recently validated in Chinese sample and showed to be a reliable and valid measure for Chinese sample and sub-clinical clients (43).

Stress coping behaviours will be measured using the short form of Coping Inventory for Stressful Situations (CISS-SFC). The CISS-SFC is a 21-item scale which measures three dimensions of coping-task-oriented coping, emotion-oriented coping, and avoidance-oriented coping. CISS-SFC has been translated into Chinese and approved to be satisfactorily valid and reliable among Chinese university students (44).

The usability and acceptance of the program will be assessed in order to gain information about users’ needs and specificities to improve interfaces of online programs for Chinese adolescents. Acceptance of the online program will be assessed by providing the users’ opportunity to write feedback at the end of each sessions. The contents of the written feedback of the online program will be evaluated. Usability will be assessed using measures such as the time they spent with the program and by the number of sessions they completed.

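### The secondary success rule asks for an increase in an undifferentiated CISS-SFC mean score, so a rise in avoidance-oriented coping counts towards success exactly as a rise in task-oriented coping does

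*Protocol*

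**What the plan says.** The protocol's Outcomes section defines success on the secondary measures as a greater fall in DASS-21 together with "statistically significant more increase in mean score of ORS and CISS-SFC in the intervention group", against control at 12 weeks. That is one instrument, one direction and no named subscale.

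The description of the instrument in the same section reads: "The CISS-SFC is a 21-item scale which measures three dimensions of coping-task-oriented coping, emotion-oriented coping, and avoidance-oriented coping". Data collection methods repeats this and adds no scoring rule, no reversed dimension and no expected direction for any of the three.

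The sentence "This study will utilize total scores in addition to subscale scores" stands in the DASS-21 paragraph and concerns that scale. Nothing similar is said for the CISS-SFC. Statistical methods says only that the secondary measures will be analysed in a similar way to the primary.

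On what the app is meant to change, the Interventions section lists "training of stress coping skills (emotion-focused coping skills and problem-focused coping skills".

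**The concern.** A rule that rewards a higher score makes sense only if a higher score on every part of the scale is what the programme is meant to produce. Here the parts are distinct ways of coping, and the protocol describes training that bears on some of them but not on avoidance. Two things can go wrong.

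- A rise in avoidance-oriented coping is credited as if it were an intended effect.
- If the three dimensions are combined into one score, a gain in task coping is partly hidden by a fall in avoidance.

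The protocol itself fixes this rule, so an analysis plan that followed it faithfully would inherit the mismatch. Because the trial is open-label, choosing a subscale or a direction after the data are in would invite the charge of selective reporting.

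**Working it through.** **The texts side by side.** The success rule gives one direction for the CISS-SFC. The description of the scale gives "three dimensions of coping-task-oriented coping, emotion-oriented coping, and avoidance-oriented coping". The Interventions section names emotion-focused and problem-focused skills. The session list in Appendix 1 covers relaxation, cognitive restructuring, problem solving, self-instruction, assertiveness, rehearsal and relapse prevention. No session sets out to increase avoidance. The rule therefore gives credit for a change that the programme is not described as producing.

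**The plan's own figure.** There is no sample size for the CISS-SFC. The figure for the primary outcome reproduces. With d = 0.43, two-sided alpha 0.05 and power 0.80, n per arm = 2 × (1.960 + 0.842)² / 0.43² = 84.9, or 85 by the normal approximation. The t-test version gives 85.87, so 86 per arm and 172 in all. Allowing for 10% dropout, 86 / 0.9 = 95.6, so 96 per arm and 192 in all. The chosen size is 300, or 150 per arm.

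**Assumptions for the illustration (not in the protocol).** Three subscales of equal SD with common pairwise correlation ρ between 0 and 0.4; 150 per arm, all observed; two-sided alpha 0.05; no clustering. The shift of 0.43 SD is borrowed from the effect size planned for perceived stress.

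**Formulas.** The SD of the sum of three unit-SD subscales is √(3 + 6ρ): 1.732 at ρ = 0 and √5.4 = 2.324 at ρ = 0.4. The effect on the overall score is d = (sum of the subscale shifts) / √(3 + 6ρ). The standard error of d is √(2/150) = 0.1155. The chance of a significant increase is 1 − Φ(1.96 − d / 0.1155).

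| True change (SD units) | d overall, ρ = 0 / 0.2 / 0.4 | Chance that the CISS-SFC criterion is met |
|---|---|---|
| Avoidance +0.43 only | 0.248 / 0.210 / 0.185 | 57.5% / 44.3% / 36.0% |
| Task +0.43 only | 0.248 / 0.210 / 0.185 | 57.5% / 44.3% / 36.0% |
| Task +0.43, avoidance −0.20 | 0.133 / 0.112 / 0.099 | 20.9% / 16.2% / 13.5% |
| Task +0.43, avoidance −0.43 | 0 / 0 / 0 | 2.5% at each ρ |
| Emotion +0.43, avoidance +0.43 | 0.497 / 0.420 / 0.370 | 99.0% / 95.3% / 89.3% |

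Worked example, first row at ρ = 0: d = 0.43 / 1.732 = 0.248; 0.248 / 0.1155 = 2.15; 1 − Φ(1.96 − 2.15) = 0.575.

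**Comparison.** The task subscale tested alone with a shift of 0.43 SD gives 0.43 / 0.1155 = 3.72 and a power of Φ(3.72 − 1.96) = 0.96.

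The first two rows are identical: an overall score cannot tell a rise in avoidance from a rise in task coping.

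**The case against.** Several counter-arguments have force.

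- **A summed total is inferred.** The protocol uses the phrase mean score for every instrument, and for DASS-21 it does not exclude subscales. The score to be derived may be settled in an analysis plan that is not at hand. This stands. If the rule is read as applying to each subscale mean, the dilution argument falls away. The other half remains: a rise in avoidance still counts as success, and a fall would count as failure.
- **The secondary criteria are joined by 'and'.** Read strictly, avoidance alone could never deliver secondary success, because DASS-21 must also fall and the ORS must rise. This stands, and the percentages above refer to the CISS-SFC criterion only. The strict reading also works the other way: a diluted CISS-SFC score could block secondary success when the other two measures improve.
- **Avoidance is never called harmful.** A reader might infer that the rule would let a harm be declared a benefit. The documents do not support that. The background says "High school students who experience negative affects and engage maladaptive coping are more likely have lower GPA", but it does not say which coping is maladaptive. What can be said is that a rise in avoidance is not a described aim.
- **The size depends on the scenario.** A reader might reach for a starker case: avoidance up 0.6 SD, ρ = 0 and 135 per arm (150 less 10%) gives d = 0.6 / 1.732 = 0.35 and power of about 80%. That shift exceeds the 0.43 planned for the primary outcome. At ρ = 0.4 it gives d = 0.6 / 2.324 = 0.26 and about 56%.

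**Conclusion.** The point holds as a mismatch between a stated success rule and the instrument to which it is applied. On either reading of the mean score, a rise in avoidance-oriented coping is credited like a rise in task-oriented coping. If an overall score is used, a task gain accompanied by a fall in avoidance is diluted.

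In the illustration, avoidance alone up 0.43 SD meets the criterion about 58% to 36% of the time. Task up 0.43 SD with avoidance down 0.20 SD meets it about 21% to 14% of the time, against about 96% for the task subscale alone. These figures rest on assumed equal SDs, assumed correlations, full follow-up and no clustering. Classes are randomised, so the true chances of detecting a real shift would be lower throughout.

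Two stronger conclusions are tempting and do not follow. The rule does not simply cancel a shift from avoidance to task coping: cancellation is complete only for equal and opposite shifts under an overall score, and the protocol states no intended fall in avoidance. Nor is the coping result beyond interpretation, since the same 21 items are collected and subscale results can be recovered. This is a correction that should be made to one secondary outcome. The primary conclusion on PSS-10 is untouched.

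**What to change.** In Outcomes, remove the undifferentiated CISS-SFC mean score from the definition of secondary success and analyse the three subscales separately. Before any outcome data are seen, state which subscale or subscales define coping success and in which direction, so that an increase in avoidance-oriented coping does not count as success.

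Task-oriented coping is the natural candidate, because it matches the problem-focused skills being trained, but the choice belongs to the investigators. Since the app also trains emotion-focused skills, they should state the direction they intend for the emotion-oriented subscale.

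The cost is about two sentences in Outcomes. Data collection and sample size do not change.

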### Participant timeline

Table 1 and Figure 2 illustrate the time schedule of enrolment, randomization, interventions, and assessments for participants.

Table 1 Perceived Stress Reduction Protocol Schedule of Forms and Procedures

|  | | | **-1** | **T0** | **T1** | **T2** |
| --- | --- | --- | --- | --- | --- | --- |
| **Activity/**  **Assessment** | **Staff**  **Member** | **Approximate**  **Time to**  **Complete** | **Pre-Study**  **Screening/ Consent** | **Pre-Study**  **Baseline/**  **Randomization** | **Post-study**  **12 weeks** | **Follow-Up**  **16 weeks** |
| Consent Form | Head teachers | 20 Minutes | X |  |  |  |
| Inclusion/  Exclusion Form | Principal investigator | 5 minutes | X |  |  |  |
| Demographics Questionnaire | Principal investigator | 10 Minutes |  | X | X | X |
| PSS-10 | Principal investigator | 10 minutes |  | X | X | X |
| DASS-21 | Principal investigator | 20 minutes |  | X | X | X |
| ORS-4 | Principal investigator | 5 minutes |  | X | X | X |
| CISS-SFC | Principal investigator | 20 minutes |  | X | X | X |
| Randomization | Principal investigator | 15 Minutes |  | X |  |  |

[figure not shown]

Figure 2 Participant Timeline

### Sample size

According to a meta-analysis on internet interventions on stress reduction (45), which reported that the overall mean effect size for stress at posttest was Cohen d=0.43 (95% CI 0.31-0.54). Significant, small effects were found for depression (Cohen d=0.34, 95% CI 0.21-0.48) and anxiety (Cohen d=0.32, 95% CI 0.17-0.47). Following this meta-analysis, we therefore choose effect sizes of d=0.43 for perceived stress, d=0.34 for depression and d=0.32 for anxiety. An absolutely reduction of 4.03 points is chosen as minimum clinically significant difference according to a previous study that analyzed PSS-10 scores in terms of minimum clinically significant important difference (MCID) (46). Based on this expected difference, no expected PSS-10 change in the control group, a population mean PSS-10 of 13.7 (SD=5.6) equal between groups (47), a sample size of 172 (n=86 in each study group) is required to detect effect size of d=0.43 with a power (1− β) of 0.80 with alpha of 0.05. A sample size of 192 (n=96 in each study group) will be needed when allowing for 10% drop out. Considering the availability of target sample, we will choose a sample size of 300 (n=150 for each study group).

### Recruitment

Participants will be recruited from grade 10 and 11 at Mianyang Dongchen International School (MDIS) and Mianyang Nanshan High School (MNHS). MDIS has a student population of more than 2000 in grade 10 and 11. MHS has a student population of more than 3500 in grade 10 and 11. More than 90 percent of high school students (total n= 4950 students) in MDIS and MHS own a mobile phone, and both schools allow students to use mobile phones on the weekends. Recruitment strategies for the trial will involve posters, flyers, advertisement and announcements in class in those two schools. Students who are self-identified as feeling stressed will be recruited. For all participants, consent forms will be read and signed by themselves, their guardians and their head teachers.

## Assignment of interventions

### Allocation

A two-arm randomized controlled trial will be conducted. Confirmed participants will be randomly allocated in a 1:1 ratio into one of the study groups. Students will be randomised within schools. In order to minimise contamination, students will be randomised on a class basis. Also, students will be notified that all of the participantas will have access to the online program, therefore they should not talk to each other about the content of the intervention. In the intervention group, the participants will use an online stress-managing program which will be delivered via smartphone. Participants in the control group will not use the online program duration. However, they will be notified that they will have access to the online program after 16 weeks (i.e., at the end of the study). The condition to which each participant will be allocated will not be blinded for either experimenters or participants.

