# Methods

## Participants, interventions, and outcomes

### Study setting

This study will be conducted in two high schools: Mianyang Dongchen International School (MDIS) and Mianyang Nanshan High School (MNHS) in Mianyang City, Sichuan Province in China. MDIS is a private school and MHS is a public school.

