### Eligibility criteria

Eligible participants include those (i) who will be enrolled in grade 10 and 11 at the beginning of the intervention; (ii) who own a smartphone and are allowed to use the smartphone during intervention period; Participants will be excluded if they (i) are intellectually impaired; (ii) are diagnosed with mental illness; (iii) are having medications which affect their mental health status (e.g., antidepressant) or attend regular counselling sessions.

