### Implementation

Clusters of students will be randomly assigned (1:1) to either the intervention of control condiction by use of computer-generated randomisation list prepared by a research assistant independent from the research groups. The participants will be enrolled by principal investigator (XZ), with the assistance of head teachers.

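### Classes are randomised within school but not within grade; if few classes take part grade could be badly unbalanced, and stratifying by grade is a cheap, minor improvement

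*Protocol*

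**What the plan says.** Under Eligibility criteria the protocol admits students "who will be enrolled in grade 10 and 11 at the beginning of the intervention". Study setting names two schools. The Allocation section fixes both the restriction and the unit: "Students will be randomised within schools. In order to minimise contamination, students will be randomised on a class basis". Implementation adds that clusters are assigned 1:1 from a computer-generated list, "by use of computer-generated randomisation list prepared by a research assistant independent from the research groups". Neither section, nor any other, names grade as a stratification, blocking or matching factor.

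Recruitment states that "Students who are self-identified as feeling stressed will be recruited", so a cluster is the set of consenting volunteers in a class, not necessarily the whole class.

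Grade is collected at baseline (Table 2) and summarised as counts and percentages. The linear mixed model under Statistical methods has group, time and group × time as fixed effects, with subject and school as random effects.

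**The concern.** If each class belongs to one grade, its grade is known before the list is made. All enrolled classmates go to the same arm, so each chance allocation moves a block of students of one grade. Randomising within school balances the schools but leaves the grade mix to chance, and with few blocks that mix can differ widely between arms.

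The intervention targets stressors from the academic environment (Interventions section), and these could develop differently in the two grades over a 12-week period. If they did, an uneven grade mix would be carried into the estimated intervention effect. An analysis plan could still adjust for grade, but nothing can restore balance once the classes have been allocated.

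**Working it through.** **The plan's own figure.** The protocol gives no figure for grade balance. Its sample size does reproduce. A two-sided t-test at alpha 0.05 with power 0.80 and d = 0.43 needs 85.87, so 86 per arm and 172 in total. With 10% dropout, 172/0.9 = 191.1, which rounds up to 192 for equal arms. Stratifying the list by grade leaves 172, 192 and the chosen 300 unchanged.

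**Inputs from the protocol.** Two schools; grades 10 and 11; 1:1 allocation of classes within school; 300 participants; pools of more than 2000 and more than 3500 pupils.

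**Assumptions, because the protocol is silent.** Each class has one grade. Clusters are of equal size. The schools contribute equal numbers of classes, half in each grade. The total number of classes is varied.

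**Formula.** With c classes per school, c/2 in grade 10 and c/2 allocated to the intervention, the number X of grade 10 classes in the intervention arm of one school is hypergeometric:

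P(X = x) = C(c/2, x) · C(c/2, c/2 − x) / C(c, c/2).

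With S = X₁ + X₂ over the two schools, each arm holds c classes, and the between-arm difference in grade 10 share is D = S/c − (c − S)/c = (2S − c)/c.

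**By hand for the two smallest cases.**
- 8 classes (c = 4): P(X = 0, 1, 2) = 1/6, 4/6, 1/6. P(D = 0) = 2·(1/6)² + (4/6)² = 18/36 = 0.50. The attainable values of |D| are 0, 50 and 100 points, so P(|D| ≥ 33) = 0.50.
- 12 classes (c = 6): P(X = 0, 1, 2, 3) = 0.05, 0.45, 0.45, 0.05. P(D = 0) = 2·0.05² + 2·0.45² = 0.41, so P(|D| ≥ 33) = 0.59.

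**At fixed thresholds across the range.**

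| Classes in total | Participants per class (300/classes) | SD of D | P(at least 33 points) | P(at least 50 points) |
|---|---|---|---|---|
| 8 | 37.5 | 0.41 | 0.50 | 0.50 |
| 12 | 25 | 0.32 | 0.59 | 0.095 |
| 24 | 12.5 | 0.21 | 0.23 | 0.044 |
| 40 | 7.5 | 0.16 | 0.03 | 0.004 |
| 120 | 2.5 | 0.09 | about 0 | about 0 |

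The rise from 0.50 to 0.59 comes from the coarse set of attainable values: with 12 classes, 33 points is the smallest non-zero difference. The SD falls steadily.

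**From imbalance to effect estimate.** Any constant grade difference in PSS-10 is present at both T0 and T1 and cancels from the group × time contrast. What remains is:

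shift in contrast = D × (difference between grades in change from T0 to T1).

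The documents give no value for the second factor. If it were 0.1 to 0.3 SD (an assumption for illustration), a 33-point imbalance would shift the contrast by 0.033 to 0.099 SD, which is 8% to 23% of d = 0.43. A 50-point imbalance would shift it by 0.05 to 0.15 SD, or 12% to 35%. If the grades change alike, the shift is 0 whatever the imbalance.

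**With school-by-grade strata.** If every stratum has an even number of equal-sized classes, D = 0. With odd strata a remainder is left. Take 12 classes, 3 per stratum, and arms kept at 3:3 within each school. If the extra grade 10 class goes to opposite arms in the two schools, grade 10 splits 3:3 and D = 0. If it goes to the same arm in both, grade 10 splits 4:2, each arm has 6 classes, and D = 4/6 − 2/6 = 33 points.

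**The case against.** Four points on the other side carry weight.

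- **Few classes may be unlikely.** Volunteers are sought from more than 5500 pupils in two schools, and 300 is about 5% of them. Eight classes would need about 38 eligible, self-identified stressed volunteers each. With class sizes of 40 to 60 (an assumption not in the documents), the pool holds roughly 5500/60 ≈ 92 to 5500/40 ≈ 138 classes, and at 120 classes even a 20-point difference has probability 0.045. This stands as a limit on the size of the problem. It does not remove it, because the protocol does not say how many classes will take part.
- **The contrast already handles a stable grade difference.** This stands: harm requires different change by grade. A reader might take the Background section as evidence of a grade effect, but it speaks of a rise from preadolescence to adolescence, not of grade 10 against grade 11. A reader might also suppose that one grade's examinations fall near week 12; the documents contain no examination calendar.
- **Randomisation remains valid without grade strata.** This also stands. The allocation is unbiased on average, and the text neither contradicts itself nor states anything false here. The point concerns the one allocation that will actually be realised.
- **Covariates are commonly left to the analysis plan.** That applies to the model terms. It does not apply to the allocation list, which the protocol fixes.

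**Conclusion.** The point holds as a minor design improvement. School is the only stated restriction, two grades are eligible and the stated model has no grade term. The chance of a difference of at least 33 points in grade share runs from 0.50 to 0.59 with 8 to 12 classes down to about 0 with 120. These figures rest on equal-sized, single-grade classes, equal numbers per school and an even grade split. Unequal numbers of volunteers per class could add imbalance.

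A reader might infer that grade will fall very unevenly between the arms, or that the intervention effect will be confounded with grade. The documents support neither. The first holds only if few classes take part, and the class count is not given. The second also needs the grades to change differently between T0 and T1, which is neither shown nor excluded. Nor is the remedy entirely free, because odd strata and extra model terms carry a small cost.

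**What to change.** - In Allocation and Implementation, state that classes will be randomised 1:1 within four strata defined by school and grade, and have the independent research assistant generate the list that way. Giving the expected number of classes there would let a reader judge how much the stratification achieves.
- In Statistical methods, add grade and grade × time as fixed effects. A grade main effect alone would not remove a difference between grades in change from T0 to T1; the interaction is what addresses it. The random effect for school need not change for this purpose.

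The cost is a sentence in the protocol, a different setting in the list generator and a few degrees of freedom in the model. In any stratum with an odd number of classes the arms may differ by one class. If there are several odd strata, the list can be constrained so that the extra classes of one grade go to opposite arms in the two schools. The sample size is unaffected.
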